## Abstract

**Background:**

Road traffic crashes for car occupants are a leading cause of death and serious injury in children from high and middle income countries globally. Correct use of appropriate child restraints can significantly reduce death and serious injury but there is a need for well powered trials to examine effectiveness of programs to increase optimal child restraint practices. The aim of this trial is to examine the effectiveness of a comprehensive intervention to increase the use of appropriate child restraints, and decrease incorrect use of child restraints in pre-school aged children traveling in cars.

**Methods and Design:**

A cluster randomised controlled trial will be conducted, involving 28 pre-school or childcare centres in low income areas of Sydney, Australia, over one calendar year. The intervention is an educational program involving an in-service for centre staff, distribution of educational materials to parents, a parent workshop demonstrating restraint use, subsidised restraints for parents in need, and vouchers for a free restraint checking service. Blinded assessors will observe restraint use at all centres at the end of the calendar year. Data will be analysed on an intention-to-treat basis; the primary analysis will compare the proportion of each of the two outcome measures (use of appropriate restraints, and incorrect use of restraints) at each centre between intervention and control groups. Detailed process evaluation will be conducted, including examination of implementation and utilisation of various elements of the program by both centres and families.

**Discussion:**

This assessor blinded cluster randomised trial is powered to provide credible evidence about the efficacy of an education and distribution program in a pre-school setting to increase appropriate use, and decrease incorrect use of child restraints.

**Trial registration:**

Australian New Zealand Clinical Trials Registry ACTRN12609000612213.

## Background

Road traffic crashes are a leading cause of death and serious injury in children in high income countries worldwide, accounting for 41% of all child injury deaths [1]. Road traffic crashes for car occupants are a leading cause of death and serious injury in Australian children. There were 461 passengers under 12 years killed in traffic crashes between 1996 and 2005 in Australia[2], and about 1000 children aged 0-14 are seriously injured each year as car occupants[3], with about a third of these aged 0-4 [4].

The effectiveness of child restraint systems in preventing injury for children involved in traffic crashes is well documented. Data from the United States showed a 28% reduction in risk of death for children aged 2-6 years using child restraints [5]. For toddlers, Zaloshnja recently reported that the adjusted odds of injury were 82% lower for toddlers in child seats than for toddlers restrained in an adult seatbelt[6]. Children aged 4-7 years using booster seats had a 59% reduction in risk of injury compared to those in adult seatbelts[7]. An in-depth crash investigation study found that for children less than 14 years of age, dedicated child restraints performed best in terms of safety, followed by lap-sash belts, then lap-only belts[8]. A recent case-control study of 152 children aged 2-8 years found no serious or fatal injuries among optimally restrained children, while 30% of sub-optimally restrained children sustained serious or fatal injuries[9]. There is therefore clear evidence that children are at substantially lower risk of serious injury and death in the event of a car crash if they are restrained in an appropriate child restraint rather than an adult seatbelt.

However, for child restraints to be effective they need to be appropriate for the age (or height and weight) of the child. Inappropriate restraint use is defined as the use of a restraint by a child who is not suitable for that restraint on the basis of their age and/or size. It is recommended that children graduate to an adult seatbelt without a booster seat when a good fit is achieved, usually once children are 145-148 cm tall (about 11 years old)[10,11]. However, many children move to an adult seatbelt too early. A recent New Zealand study found that only 40% of children requiring a booster seat were using one, and in the 5-8-years age group, 93% required a booster seat but only 30% were using one [12]. Other studies have shown that inappropriate restraint is highest among children aged 2-8 years [13-15]. Recent Australian research showed that, of children meeting the booster seat height-weight criteria, 56% had been prematurely graduated into an adult seat-belt[16].

Factors that have been associated with premature graduation from one restraint type to another in recent Australian studies include low parental education [16-18], poor parental knowledge of appropriate restraint transition points [18], larger families [16,18], older age of child [18], travelling in other people's vehicles and parenting style [18]. Studies conducted in the US have identified perceived restraint comfort, lower income status and educational attainment as factors associated with a higher risk of early graduation to a seatbelt-only restraint [19,20].

Although children may be restrained in an age-appropriate child restraint, incorrect use of restraints can also degrade the level of protection provided in a crash. Incorrect use is when the restraint system is not used as intended and can occur in both child restraints and adult seatbelts with or without booster seats. Examples include incorrect positioning and/or tension of the belt and incorrect attachment of the restraint to the vehicle. Incorrect restraint use substantially increases injury risk. In its most serious form, an incorrectly used restraint may fail to control the child's motion in a crash, leading to impact with the vehicle interior and other occupants. An Australian retrospective case review of 2-8 year olds in crashes found that children incorrectly using restraints were 6.9 times more likely to be seriously injured than those correctly using their restraints, irrespective of restraint type [9]. More recent work has shown that 51% of children in the state of New South Wales (NSW) are incorrectly restrained, with the prevalence of incorrect use highest among those using dedicated child restraints (65% of those using forward facing restraints and 60% of those using booster seats, compared to 48% of those using adult seatbelts). In addition, the data have shown that the forms of incorrect use were more serious for children restrained in seatbelt, booster seats and harnesses, all typically used by children in the 3-6 year age group [21]. Risk factors for incorrect use of child restraints include lower educational levels, families who remove the seat frequently from their vehicle, drivers who are not the parent of the child, and young, small children [22]. Incorrect use of booster seats is more likely to occur in children from low socioeconomic and non-English speaking background (NESB) families [23].

Previous research has predicted that the greatest gains are to be made by targeting both the use of appropriate restraints and the correct use of restraints [24]. Studies have also demonstrated the effectiveness of various interventions to increase child restraint use. A recent systematic review [25] found that incentives or the provision of a free child restraint combined with education increased the use of restraints - but concluded that, although the interventions seemed promising, there was a need for high quality well-controlled studies to evaluate effectiveness of programs aimed at increasing use of child restraints. A recent US trial found that a pre-school based intervention to increase restraint use was not effective but also reported that few families received the intervention as planned [26]. Intervention studies aimed at decreasing incorrect use of restraints are less common, with only one published study, which showed an education program was effective in increasing correct use of restraints [27]. There have been no Australian trials examining effectiveness of interventions to increase the use of appropriate child restraints or decrease incorrect use of child restraints.

There is a clear need for a well powered trial of interventions aimed at improving the quality of restraint use. Given the lack of effectiveness of previous trials, there is also a need to understand clearly the process aspects of the trial.

The aim of this trial is therefore to examine the effectiveness of a comprehensive intervention to 1) increase the use of appropriate child restraints and 2) decrease incorrect use of child restraints in pre-school aged children travelling in cars.

## Methods

The study is a cluster randomised trial, designed in line with the CONSORT statement [28], with randomisation of 28 pre-school or childcare centres. Eligible centres will be identified from early childhood education services in the Sydney metropolitan area via the Kids and Traffic program at Macquarie University who provide road safety education services to all pre-schools and childcare centres state-wide. Directors of eligible centres will be approached by mail and phone by research staff to participate in the trial. Once the directors have consented to join the study and to be randomised, randomisation will occur into treatment and control groups.

Eligible centres will include community pre-schools or childcare centres with a minimum of 20 families with a child in the eligible age range (3-5 years). Children with their 3^rd ^birthday in 2010 and older will be included as inappropriate use begins to increase dramatically from this age and 3 year old children are widely enrolled in pre-school programs. Because interventions are most needed in families from low educational backgrounds, eligible centres will be those based in local government areas (LGA) of Sydney metropolitan area ranked in the lowest 30% of LGAs in the Sydney Metropolitan Area according to the Socioeconomic Indices For Areas (SEIFA): Index of Education and Occupation scores (SEIFA scores <980). LGAs to be included are Fairfield, Campbelltown, Liverpool, Blacktown, Canterbury, and Bankstown. English must be used as the instructional language in the centre and physical layout of the centre and parking must allow for safe observation of vehicles upon arrival, without major disruption to traffic flow. Finally, centres must have no active engagement or specific policies on child restraints, or programs where they actively engage with families on this issue. A complete list of eligible centres will be created, stratified by service type (pre-school or long daycare), and each will be allocated a unique identifier. The centres will be approached in random order until enough centres of each service type have been recruited. The number of each service type will be chosen to match the distribution of service types in these areas, with an even number of each type and totalling 28. An authorised representative of the centre will sign a record of informed consent.

A baseline assessment will be conducted before randomisation to determine whether the control and intervention groups have similar baseline restraint use patterns. While direct observation of children in situ would be the best way to measure baseline levels of appropriate restraint use, such observation and necessary contact with research assistants may in itself act as an intervention. To avoid such potential contamination of the control group, baseline measures will therefore involve a brief self-report questionnaire to be completed by parents/guardians in both intervention and control centres when they sign children in or out of the centre. Information will be collected about number of children in the family, age of children, type and frequency of restraint use and seating position in car. Although this technique will be less accurate than the direct observations made post intervention, previous work has shown that parent interview tools may be used to accurately describe child restraint use [29], and it has been determined that the risk of measurement error is less important than any possible contamination of the control group which may occur by more detailed measures. This process will also remove any ethical dilemmas that may arise if children in the control group were observed to be restrained inappropriately. Any self-report bias should be similar between groups.

Restricted randomisation will be conducted using the unique identifiers and summary data from the baseline survey to ensure adequate balance of important factors. The five balance criteria will be (i) service type exactly balanced between groups; (ii) self-reported restraint choice for the 3-5 year-old children attending the service (proportion appropriately restrained): mean proportions in each group differ by no more than 5% in relative terms (i.e. ratio of means between 0.95 and 1.05); (iii) mean proportion of families with annual household income below AU$60,000 in each group differ by no more than 10% relatively; (iv) mean proportion of families who speak a language other than English at home in each group differ by no more than 10% relatively; and (v) mean size (number of children aged 3-5 years enrolled) of centres in each group differ by no more than 10% relatively. The randomisation process will be fully concealed as the statistician will allocate the centres at a site remote to the recruitment site and will only have access to a list of centres recruited. Of the 28 centres in the study, 14 centres will be randomly allocated to each of the intervention and control groups.

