### Sample size and statistical analysis

This study has 80% power to detect a 20% increase in use of appropriate child restraints from 60% to 80%, as significant at the 5% level. Previous research has indicated that educational and incentive based interventions may increase use of restraints by about 20% [25]. In NSW the use of appropriate child restraints in 20 centres in Sydney varied from 30-70% [31]. However, among centres from local government areas with low educational attainment, the average use of appropriate child restraint use is 30-40%. If the effect of the implemented RTA general marketing program raises the base rate in controls to 60%, the study will be adequately powered to find an effect of a 20% increase. However, it will also have power to detect a 20% effect if the base rate of restraint use remains between 30-50%. Increasing the rate to 80% is feasible: the base rate of child restraint use in centres in areas with high education and high socioeconomic status is around 70%, so this increase is possible. Previous work has allowed estimation of the intra-class correlation as 0.06, based on proportion using appropriate restraint at 9 centres [31]. Allowing for a minimum of 20 eligible children at each centre (with an average number of slightly more than 20 anticipated) would require 20 centres. Further allowing for 30% centre drop-outs through the course of the study requires 14 intervention centres and 14 control sites. This sample size will also allow 80% power to establish whether incorrect use of restraint systems can be reduced from 60% of children using restraints to 40%. Direct observation of children in pre-school settings in Sydney found that 65% of children using forward facing child restraints and 60% of children in booster seats were incorrectly using the restraints [31].

Data will be analysed on an intention-to-treat basis. The primary analysis will compare the proportion of each of the two outcome measures (appropriateness and correctness of restraint use) at each centre between the intervention and control groups using Donner's adjusted chi-square test[32]. Logistic regression modelling will be used to explore predictors of each outcome measure, using generalised estimating equations (GEE) to allow for clustering of data by centre.

The study protocol was approved by the Human Research Ethics Committees of the University of Sydney and the University of NSW.

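### The primary comparison leaves out child age, which the protocol records and links to both outcomes; a pre-specified age adjustment would be a cheap, modest gain, chiefly for incorrect use

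*Protocol article*

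**What the plan says.** The Background of the protocol article lists factors associated with moving too early to the next restraint type; one is "older age of child [18". The Methods justify the lower age limit partly because "inappropriate use begins to increase dramatically from this age". For incorrect use, the risk factors in the Background include "drivers who are not the parent of the child, and young, small children [22". So the article names age for both outcomes, in opposite directions, as one factor among several and without an effect size.

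Age is available. In the baseline questionnaire, "Information will be collected about number of children in the family, age of children, type and frequency of restraint use", and the interview at outcome observation records the child's age again.

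Neither the allocation nor the primary test uses it. "The five balance criteria will be (i) service type exactly balanced between groups"; the other four are baseline appropriate restraint, household income, home language and centre size, and size counts children without regard to age. Criterion (ii) requires that "mean proportions in each group differ by no more than 5% in relative terms (i.e. ratio of means between 0.95 and 1.05". Under Sample size and statistical analysis, each outcome is compared "between the intervention and control groups using Donner's adjusted chi-square test". Logistic GEE models are planned only to explore predictors.

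**The concern.** Where a trial names a predictor of both primary outcomes, holds it for the children observed, and has only 20 to 28 centres, one expects it in the primary comparison. Leaving it out has two costs. Predictable variation stays in the error term. And an arm that happens to have younger children will tend to look somewhat better on appropriate use and somewhat worse on incorrect use, with nothing in the primary test to separate age from the programme.

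The two outcomes are not equally exposed. Appropriate use has a baseline version that the randomisation balances. Incorrect use has no baseline measure, so no criterion is aimed at its age component.

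**Working it through.** **1. The plan's own figure.** Inputs from Sample size and statistical analysis: 60% against 80%, 80% power, 5% level (taken as two-sided), ICC 0.06, 20 children per centre.
- Design effect: 1 + 19 × 0.06 = 2.14.
- Two proportions with continuity correction: 91 per arm; 91 × 2.14 = 194.7; 194.7 / 20 = 9.74, so 10 centres per arm, or 20 in all. This matches the stated figure. Without the correction, 82 per arm gives 8.77, so 9 per arm.
- Drop-out: 20 / 0.7 = 28.6, against 28 stated.
- Standard error of the arm difference at 14 centres (280 children) per arm: appropriate use √[(0.6×0.4 + 0.8×0.2) × 2.14 / 280] = 5.5 points; incorrect use, 60% to 40%, √[(0.6×0.4 + 0.4×0.6) × 2.14 / 280] = 6.06 points.

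**2. How far a chance age difference can move an estimate.** The documents give neither an age gradient nor the spread of age mix between centres, so both are assumed. Half the children count as older. The true share of older children varies between centres with SD b from 0 to 0.20. The older-versus-younger contrast d runs from 10 to 30 points. With 20 children per centre, the SD of a centre's observed share is s = √[b² + (0.25 − b²)/20]. With k centres per arm, the SE of the share difference is s√(2/k), and the shift is d times that.

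| b | d (points) | k | SE of share difference | 1-SE shift | 1.96-SE shift |
|---|---|---|---|---|---|
| 0 | 10 | 14 | 0.042 | 0.42 | 0.83 |
| 0.10 | 20 | 14 | 0.056 | 1.12 | 2.20 |
| 0.20 | 30 | 14 | 0.085 | 2.55 | 4.99 |
| 0 | 10 | 10 | 0.050 | 0.50 | 0.98 |
| 0.10 | 20 | 10 | 0.066 | 1.33 | 2.60 |
| 0.20 | 30 | 10 | 0.100 | 3.01 | 5.91 |

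**3. Type I error.** Simulation, 4,000 trials per setting, 14 + 14 centres, d of 20 or 30 points, b of 0.10 to 0.20, with a centre-level t-test standing in for the adjusted chi-square (simulation error about 0.35 points).
- With criterion (ii) applied: 2.0–2.7% for appropriate use, 4.7–5.2% for incorrect use.
- With no restriction, which is not the plan: 4.5–6.0% and 4.6–5.3%.
- Criterion (ii) hardly narrows the age difference itself. At b = 0.15 and d = 20 the SD of the share difference is 0.056 with and without it; in the steepest setting it falls from 0.075 to 0.071. The protection comes through the baseline outcome, not through age.

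**4. What adjustment gains.**
- Appropriate use, simulation of 1,500 trials per setting with criterion (ii) applied. Assumptions: three equal birth cohorts, appropriate use falling 10–20 points per year of age, centre mean age with SD 0.15–0.25 years, total between-centre variance 0.06 × 0.24, true effect 15 points. Age adjustment changed the variance of the arm difference by between a 0.2% increase and a 10% reduction. Power rose by about 1 to 8 points, for example from 50.7% to 54.9% with 20 centres, 15 points per year and SD 0.25.
- Incorrect use was not in that simulation. A ceiling follows from steps 1 and 2, as the squared ratio of the 1-SE shift to the design SE at 14 per arm: (0.42/6.06)² = 0.5%, (1.12/6.06)² = 3.4%, (2.55/6.06)² = 17.7%. This is the most that adjustment could remove if the gradient were known. It passes 10% only with the 30-point contrast and b of 0.15 or more.

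**The case against.** The strongest reply is that allocation is random. A chance age difference is then sampling error, not bias, and the ICC of 0.06 was based on proportions at nine centres, so variation in age mix is presumably already inside it. This stands, and step 3 bears it out. A reader might infer from the opposite gradients that leaving out age distorts both primary results; the documents do not support that.

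Nor do they support reading age as what drives the outcomes. It is one listed factor for each, without a size. For incorrect use no gradient within ages 3 to 5 is given. The Background's remark that errors were more serious in the restraints typical of ages 3 to 6 concerns severity, not prevalence, so it neither establishes nor cancels a gradient.

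A reader might also infer that an age imbalance could pass for programme success. On the protocol's own directions it helps one outcome and hurts the other, so it cannot mimic improvement in both. It could resemble the pattern that the Discussion hopes to offset, more appropriate use with more incorrect use, but only by the few points shown.

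Criteria (i) and (ii) already give partial protection, chiefly for appropriate use. That stands, and it narrows the point to incorrect use.

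Finally, an unadjusted primary test is a legitimate choice, and covariate lists are often left to an analysis plan that is not shown. That holds for the exploratory models. The primary method, however, is stated in the article and has no place for age.

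**Conclusion.** The point holds as a low-cost improvement, not as an error that affects validity. Age is named for both outcomes, recorded twice, and used in neither the restriction nor the primary comparison. There is no expected bias, and under the planned restriction simulated type I error stays near or below 5%. A chance imbalance would typically move an estimate by 1 to 3 points, and by about 5 to 6 under the most extreme assumed gradients, against a planned 20. The simulated variance reduction from adjustment is about 0–10%. All these sizes rest on assumed gradients and an assumed spread of age mix, and the simulated reduction is for appropriate use only. For incorrect use, where the gap mainly lies, there is only the ceiling in step 4: 3.4% in the middle case.

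**What to change.** Under Sample size and statistical analysis, pre-specify that each primary comparison is adjusted for the child's age at observation. One way suited to few centres: fit a child-level logistic model containing age but not arm, take observed minus expected for each centre, and compare these centre-level residuals between arms. Report the unadjusted Donner chi-square result alongside. State this before outcome data are seen, so that the choice cannot look driven by the results.

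The cost is one covariate already collected and a simple rule for children of unknown age.

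An age-mix criterion in the restricted randomisation, such as mean age of eligible children within a stated tolerance, is optional. It would leave fewer acceptable allocations. It is also indirect, because it balances questionnaire respondents before randomisation rather than the children observed later at drop-off. Adjustment at analysis deals with the observed children directly.
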